### Assignment of Interventions

Patients are randomized 1:1 at inclusion to either the 12-month or 6-month intervention group. According to the risk of nonadherence due to the adverse effects of statins or the complexity of the drug regimen, 4 randomization groups were created: patients treated with statins, patients who have to take at least one drug more than once daily, patients with both of the former conditions, and patients with none of the former conditions. Then, the randomization is performed in each strata and is coded with 0, corresponding to group A, where patients receive the intervention for 12 months, or 1, corresponding to group B, where patients receive the intervention for 6 months. The randomization code is generated by a random repetition of 4 and 6 blocks composed of 1 or 0 (Excel, Microsoft) to prevent predictability of the sequence. The randomization sheets were created by an independent researcher from the Unisanté Research Support Unit. The allocation is established for each consecutive patient by unsealing the randomization sheet. This study is open, and the clinical team as well as the patients are aware of the allocation group.

### Outcomes

#### Primary Outcomes

The global adherence outcome is defined as the percentage of days a patient correctly takes the medication across the individual study duration. The mean global adherence will be compared between groups. According to the EMERGE (ESPACOMP Medication Adherence Reporting Guidelines), medication behaviors will also be described longitudinally in both groups through 3 operational definitions: implementation, persistence, and longitudinal adherence at 6, 12, 18, and 24 months after enrolment [23].

#### Secondary Outcomes

The ADVANCE and UKPDS clinical scores will be assessed and compared at baseline, 6, 12, 18, and 24 months after enrolment for patients with type 2 diabetes in both groups. The ADVANCE score indicates the risk of developing cardiac complications associated with type 2 diabetes within 4 years and estimates the risk of developing renal complications within 5 years or more than 5 years. The UKPDS score calculates the risk of fatal coronary heart disease or stroke in patients with type 2 diabetes with no antecedent cardiovascular disease. These scores are calculated on the following parameters: sex, ethnicity, smoking status, time since diabetes diagnosis, blood pressure, glycated hemoglobin, total and high-density lipoprotein cholesterol, atrial fibrillation, albumin in urine, abdominal circumference, and BMI [24].

During the postintervention monitoring phase, the number of patients with less than 30% adherence for at least one drug during 2 consecutive visits as well as the time-to-event will be compared between the groups. We will also describe implementation and persistence at 6 months and 12 months after the end of the intervention in both groups to explore the impact of the length of the intervention on adherence. Patient satisfaction regarding the program will be analyzed through qualitative interviews.

#### Sample Size

An expert committee composed of nephrologists, endocrinologists, nurses, pharmacists, and statisticians agreed that the difference in the mean global adherence between groups should be 5%. The hypothesis states that the adherence rate will average 97.5% in the 12-month intervention group and 92.5% in the 6-month intervention group. A standard deviation of 1.7 was assumed in the logit scale in both groups. This corresponds to 95% global adherence in the intervals (57.5%-99.9%) and (30.0%-99.7%) for the 12-month intervention group and the 6-month intervention group, respectively. According to these parameters, a sample size calculation was made simulating individual series of daily medication (1=at least the correct number of daily openings of the electronic monitor for all drugs monitored; 0=fewer daily openings than prescribed for at least one drug monitored), in order to consider both the interindividual variability (SD 1.7) and the intraindividual variability (the measurement error). Considering that the mean number of measures of a subject will be 365, 72 patients must be included in this study (36 participants in each group) to have a power of 80% and a two-tailed alpha error of .05. Regarding the qualitative study, the expert committee agreed that a subgroup of 14 included patients will attend the qualitative interview but more patients may be included if data saturation is not reached after the completion of 14 interviews.

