#### Medication Adherence

All dates and the timing of electronic monitor activation will be used to analyze medication adherence. Electronic monitor data will be reconciled with pill counts and patient reports [26]. The global adherence will be calculated as the percentage of days during which the drug is taken properly across the individual study duration. Two-sided Student *t* test will be used to compare the mean probabilities between groups in the logit scale. A difference between groups will be considered statistically significant if *P*<.05. Medication behaviors are characterized by implementation, persistence, and longitudinal adherence [27].

Implementation evaluates at each day the proportion of patients taking at least the correct dose prescribed on that day among the patients who are still participating in the program. For each participant, the daily medication behaviors will be described with a binary variable (1=at least the correct number of daily openings of the electronic monitor for all drugs monitored; 0=fewer daily openings than prescribed for at least one drug monitored). This code is commonly used and cannot discriminate overadherence, which will be considered as adherence. Implementation will be modeled with the generalized estimating equation multimodeling [28].

Persistence corresponds to the distribution of times between inclusion in the study and discontinuation (ie, unilateral stopping of treatment by the patient). Persistence will be described with a Kaplan-Meier survival curve. The log rank test will be used to compare the persistence between groups [28].

Longitudinal adherence is defined at each day as the proportion of patients taking at least the correct dose prescribed on that day among all the patients included in the study. Longitudinal adherence will be presented as the product of persistence and implementation and modelized by generalized estimating equation multimodeling [28]. In an exploratory analysis, univariable and multivariable regressions will analyze the associations among medication behaviors (combining persistence and implementation), sociodemographic and clinical data at inclusion, and changes in the clinical and biochemical variables at the completion of the study.

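### The 97.5% and 92.5% behind the sample size act as medians, not averages: with the stated logit SD they imply a gap of 8.2 points in mean adherence, not 5

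*Protocol article*

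**What the plan says.** Under Primary Outcomes, the protocol article defines global adherence as the percentage of days with correct intake over a patient's time in the study, and says that its mean will be compared between groups.

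The Sample Size section then sets the target and the inputs:

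- The committee "agreed that the difference in the mean global adherence between groups should be 5"%.
- The hypothesis is that "the adherence rate will average 97.5% in the 12-month intervention group and 92.5% in the 6-month intervention group".
- On spread: "A standard deviation of 1.7 was assumed in the logit scale in both groups".
- It adds the range that this implies: "This corresponds to 95% global adherence in the intervals (57.5%-99.9%) and (30.0%-99.7"%), for the 12-month and 6-month groups in that order.
- The calculation simulated daily binary intake, with 365 daily values per patient on average. Its result is that "72 patients must be included in this study (36 participants in each group"), for 80% power at a two-sided alpha of 0.05.

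Under Data Analysis, Medication Adherence, a two-sided t test "will be used to compare the mean probabilities between groups in the logit scale".

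Nowhere does the article call 97.5% and 92.5% medians or back-transformed logit means.

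**The concern.** A logit-normal variable with SD 1.7 and a centre above 90% is strongly skewed to the left, so its mean lies well below its median. The text speaks of averages and of a difference in means, while the spread and the test are on the logit scale. If the two percentages were placed at the centre of the logit distribution, they are not averages of adherence, and the 5 points are not a difference in means.

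The 5 points are the committee's benchmark, and the outcome is described as mean global adherence. A reader will naturally set the observed difference in mean adherence against 5 points and assume that the trial had 80% power for it. That comparison is sound only if the planned difference is a difference in means.

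**Working it through.** **Inputs**, all from Sample Size: 97.5% and 92.5%; logit SD 1.7 in both groups; 36 per group; two-sided alpha 0.05; 365 days per patient on average. Subject-level adherence is taken as normal on the logit scale, as the SD and the intervals imply.

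**1. Reproduce the sample size with the values as logit centres.**
- logit(0.975) = ln(0.975/0.025) = 3.664
- logit(0.925) = ln(0.925/0.075) = 2.512
- Difference 1.151; odds ratio exp(1.151) = 3.16; standardised difference 1.151/1.7 = 0.677
- The two-sample t test needs 35.2 per group for 80% power, hence 36. Power at 36 is 80.9%.
- A simulation of 20,000 trials (365 binomial days per patient, empirical logit with a 0.5 correction, t test) gives about 78–79%.

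The stated 36 per group is reproduced.

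**2. Reproduce the printed intervals.** Formula: expit(centre ± k × 1.7).

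| Reading | 12-month | 6-month |
|---|---|---|
| Printed | 57.5%–99.9% | 30.0%–99.7% |
| Values as logit centres, k = 1.96 | 58.2%–99.9% | 30.6%–99.7% |
| Values as logit centres, k = 1.98 | 57.4%–99.9% | 29.9%–99.7% |
| Values as logit centres, k = 2 | 56.6%–99.9% | 29.2%–99.7% |
| Values as arithmetic means, k = 1.96 | 82.9%–99.97% | 55.0%–99.9% |

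The last row uses the centres that would make the arithmetic means 97.5% and 92.5%: 4.908 and 3.534, or medians of 99.3% and 97.2%. Their difference of 1.374 would need only 25–26 per group. So both the intervals and the sample size fit the reading as logit centres, and neither fits the reading as means. Because expit is monotone, a centre on the logit scale is a median on the percentage scale.

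**3. The means that the inputs imply.** Mean adherence is the integral of expit(μ + 1.7z) over the standard normal density.
- μ = 3.664 gives 93.2%, which is 4.3 points below the median of 97.5%.
- μ = 2.512 gives 85.0%, which is 7.5 points below the median of 92.5%.
- Difference before rounding: 93.19 − 84.95 = 8.24, or 8.2 points.

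**4. Power for a 5-point difference in arithmetic means.** SD 1.7 and 36 per group throughout. For each pair, the centres with those means were solved for, and the t-test power was computed without and with day-level noise.

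| Means | Logit difference | Power with noise | Power without noise |
|---|---|---|---|
| 90% vs 85% | 0.61 | about 31–32% | about 33% |
| 93.2% vs 88.2% | 0.78 | about 45–46% | about 48% |
| 95% vs 90% | 0.93 | about 60% | about 63% |
| 97.5% vs 92.5% | 1.37 | about 89% | about 92% |

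The first three pairs are illustrations and are not in the article. The second keeps the 12-month mean that the article's inputs imply, and the first keeps, to rounding, the implied 6-month mean. The fourth takes the article's words literally but contradicts its printed intervals.

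**The case against.** The strongest reply is that nothing in the design is wrong. The SD, the intervals, the simulation and the test are all on the logit scale and agree with one another. At the planned logit difference, 36 per group give the stated power to within a point or two. What is left is a loose label, and the printed intervals let a careful reader recover its meaning. All of this stands, except that the label is the one attached to the outcome and to the committee's benchmark, so it is worth correcting.

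A reader might infer that the trial is underpowered for a 5-point difference in means. The article does not support that as a general statement. At a fixed logit SD, power for a 5-point gap depends wholly on where the means lie, and if the true means were 97.5% and 92.5% it would exceed 80%. Quoting only the low figures would mislead. Equally, the high figure cannot be used to defend the wording, because it needs distributions other than those printed.

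A reader might also see a second error in the Data Analysis sentence, since a t test on logits does not compare mean probabilities. That sentence states that the comparison is made in the logit scale. It is awkward wording, not a wrong method.

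Finally, the article plans no conclusion from a null result, so misreading one is a risk for later reporting and not a flaw in the plan.

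**Conclusion.** The planning figures are mislabelled. By the article's own intervals and sample size, 97.5% and 92.5% are medians (back-transformed logit means). The difference in mean global adherence that they imply is 8.2 points, against the stated 5. The 80% power attaches to a logit difference of 1.15, odds ratio 3.2, and should not be read as 80% power for a 5-point difference in means.

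The number of patients is right for the planned test. The conclusion rests on normality on the logit scale with SD 1.7 in both groups. Which quantity the committee had in mind for its 5 points, median or mean, cannot be told from the article; the text says mean and the calculation used the median.

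**What to change.** - In Sample Size, state that 36 per group give about 80% power for median adherence (back-transformed logit mean) of 97.5% versus 92.5%, odds ratio 3.2, and that with a logit SD of 1.7 this corresponds to mean adherence of 93.2% versus 85.0%. Describe the 5 points as a difference in medians.
- Report the primary t-test result as a logit difference or odds ratio with its confidence interval, with back-transformed values labelled as such. Show arithmetic mean adherence descriptively.
- Do not present the result as a test with 80% power for a 5-point difference in means. If power for such a difference is quoted, name the means assumed and show the range.

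The cost is wording only. Recruitment has closed with 73 patients, and neither the sample size nor the test changes. The article has the statistician unaware of allocation until the data are frozen, so the labels can be settled before the groups are known.

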#### Participant Timeline and Data Collection

Data collection is performed by the investigators and is prospectively registered in the platform Research Electronic Data Capture (RedCap), a secure web app for building databases. Each patient has a unique study number generated by RedCap. First, during recruitment, if eligible patients refuse to participate, their reasons for doing so are recorded. For patients included in this study, their sociodemographic data are provided by the administrative software of the hospital at inclusion. Clinical data for each visit are provided by the patient electronic clinical file (Soarian, Cerner) and reported in the case report form. The participant timeline and data collection process are shown in Multimedia Appendix 2 [25] for both groups. Electronic monitor data are uploaded on the secured MedAmigo web portal at each medication adherence visit during the intervention and at each medication refill during the follow-up for both groups. Concomitantly, the patient’s electronic monitor use is systematically checked by the pharmacist through a set of validation questions (ie, identification of nonmonitored periods, eg, during hospitalizations, whether medication was sometimes prepared in advance for a later use since the last visit). A pill count is performed by the technician during the intervention phase and by a blinded independent researcher during the postintervention monitoring phase. The participants who leave this study before completion are not replaced and are considered as dropouts but the data collected until then will be kept for analysis. The data monitoring committee is composed of the main investigators of the PANDIA-IRIS study. After the end of this study analysis, data will be archived and kept for 10 years in the secure data warehouse of the University Hospital before destruction. The database of the PANDIA-IRIS study will be shared in a secured data repository of the University of Geneva (Yareta) at the end of the analysis.

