#### Medication Adherence Intervention

All included patients will benefit from the IMAP in addition to routine clinical care. The frequency of IMAP visits is the same in both groups throughout the 24 months: once per month for the first 3 months, followed by 1 visit every 3 months (Figure 1). Pharmacists lead short, repeated semistructured motivational interviews based on the theoretical Fisher model [22]. First, patients’ knowledge of treatments is evaluated. Then, motivation to take the treatment, self-efficacy, daily medication behaviors, and side-effect management are explored in an empathetic nonjudgmental way. The graph representing electronic monitor daily openings (dates and hours) since the last visit is shown to the patient as feedback. Adherence results are discussed to reinforce acquired adherent behaviors and to understand nonadherent episodes, and then, solutions with tailored elements are constructed to address nonadherence. To ensure interprofessional collaboration, the pharmacist sends a semistructured report after each medication adherence interview to the clinical team, including the endocrinologist, nephrologist, general practitioner, nurse, dietician, and psychologist. During the COVID-19 pandemic, adherence interviews are conducted through phone calls for some patients, if the clinicians considered them at high risk of complications following infection by SARS-CoV-2. If the interview is conducted by phone, it is notified on the case report form.

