### Postintervention Monitoring Phase

After the intervention phase, patients will still use electronic monitors with their LCD screens, but their adherence data will be double-blinded. Patients will not receive any feedback or motivational interviews about their daily drug management. The clinical team will not obtain any adherence reports. Due to ethical reasons, if the medication adherence rate detected by the MedAmigo software is less than 30% for at least one drug for 2 consecutive pharmacy visits, the software will automatically notify the pharmacist, and the patient will stop the study and will be oriented to the routine IMAP. If a physician in charge of a patient explicitly asks to access the adherence data during the postintervention monitoring phase for clinically urgent and important reasons, the principal investigator will sign a permission form that will be included in the case report form, and the patient will stop the study. All the data collected until then will be kept for analysis. At 18 months after the inclusion, during the postintervention monitoring phase, blood and urine samples will be collected to determine the clinical values at this time point. Indeed, the frequency of blood and urine samples collection differs between patients, and collecting laboratory values for each patient at this precise time point will ensure consistency in the analysis.

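### The article does not settle when monitors are read after the intervention; if reads follow refills, the under-30% outcome can be detected late or missed in some of the least adherent patients

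*Protocol article*

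**What the plan says.** Four sections of the protocol article bear on this.

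- **Participant Timeline and Data Collection:** monitor data are to be "uploaded on the secured MedAmigo web portal at each medication adherence visit during the intervention and at each medication refill during the follow-up for both" arms.
- **Medication Adherence Intervention:** "The frequency of IMAP visits is the same in both groups throughout the 24 months", namely "once per month for the first 3 months, followed by 1 visit every 3 months".
- **Postintervention Monitoring Phase:** "Patients will not receive any feedback or motivational interviews about their daily drug management". If the adherence rate "is less than 30% for at least one drug for 2 consecutive pharmacy visits, the software will automatically notify the pharmacist", and the patient then leaves the study, with data up to that point kept.
- **Secondary Outcomes:** the groups are compared on "the number of patients with less than 30% adherence for at least one drug during 2 consecutive visits as well as the time-to-event". Under Data Analysis, Medication Adherence, the count is tested by chi-squared or Fisher exact test.

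Monitoring lasts 24 months in both groups, so the postintervention phase lasts 24 − 12 = 12 months in group A and 24 − 6 = 18 months in group B. Up to six drugs are monitored per patient. The article gives no days' supply per refill. It refers to Figure 1 for the visits and to Multimedia Appendix 2 for the data collection timeline; neither was available for this review.

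**The concern.** The software can flag only data that have been uploaded. If uploads happen at refills, and a patient returns when the pills run out, then the number and timing of reads depend on the adherence being measured. A patient who takes few pills comes back rarely, and one who stops refilling produces no read at all. The event would then be hardest to see where it is most certain to be present, and its date would reflect pack size and refill habit as well as behaviour.

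At stake are one between-group secondary outcome (count and time to event) and the alert that the article describes as an ethical safeguard. The follow-up phases differ in length, so any missed detection need not be equal in the two groups.

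**Working it through.** The article states no figure for this outcome or its timing, so there is nothing of its own to reproduce. The check is of the text, then of the size under a stated assumption.

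**1. The sections side by side.** The data collection section treats an adherence visit and a refill as two different occasions and assigns postintervention uploads to the refill. The intervention section has programme visits continuing every 3 months to month 24. The postintervention section removes interviews and feedback but still speaks of pharmacy visits. Read literally, the first gives refill-driven reads and the second gives calendar reads.

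**2. Formula for refill-driven reads.** Inputs:

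- S = days' supply per refill (assumed 30, 60 or 90)
- r = days' supply left at the start of the phase (assumed between 0 and S)
- a = adherence, the same for every monitored drug
- T = phase length, about 365 days (A) or 548 days (B)

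If the patient returns when the supply is used up, the first read is at r/a days and the second at (r + S)/a days. Two reads fit in the phase only if a ≥ (r + S)/T.

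**3. Day of the second read (r = 0 to r = S).**

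| S | a = 29% | a = 20% | a = 10% |
|---|---|---|---|
| 30 | 103–207 | 150–300 | 300–600 |
| 60 | 207–414 | 300–600 | 600–1,200 |
| 90 | 310–621 | 450–900 | 900–1,800 |

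For example, 30/0.29 = 103 and 60/0.29 = 207; 90/0.29 = 310 and 180/0.29 = 621.

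**4. Lowest adherence at which two reads fit, (r + S)/T.**

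| S | Group A | Group B |
|---|---|---|
| 30 | 8.2–16.4% | 5.5–10.9% |
| 60 | 16.4–32.9% | 10.9–21.9% |
| 90 | 24.7–49.3% | 16.4–32.8% |

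A patient below the relevant figure cannot meet the two-visit rule within the phase. The limit is higher in group A because its phase is shorter.

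**5. Dependence on r.** At a = 29% and S = 90, the second read falls inside the phase if r ≤ 0.29 × 365 − 90 ≈ 16 days (A) or r ≤ 0.29 × 548 − 90 ≈ 69 days (B).

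**6. Cases in which the delay disappears.** If another monitored drug is taken at 95% and all monitors are read at its refill, then even from a full pack the second read is at 2S/0.95 = 63, 126 or 189 days for S = 30, 60 or 90. If reads are on the calendar every 3 months (about 91 days), the second read is at about 182 days whatever the adherence.

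**The case against.** No section says that refills follow consumption or that patients return only on an empty pack. A 3-monthly pharmacy visit at which medication is supplied, without an interview, would satisfy all three sections, though calling it a programme visit would then be loose wording. The pill count kept in the postintervention phase fits planned refills with leftover pills. The timeline appendix may settle the matter. This stands in part: it makes the delay conditional. It does not remove the disagreement in the text, because the data collection section separates adherence visits from refills and names only the latter for follow-up.

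Three stronger readings are tempting, and the documents do not support them:

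- *Every poorly adherent patient is detected later.* The rule needs only one drug below 30% out of up to six. A well-taken drug can bring the patient in on time.
- *With 90-day supplies the rule can never be met below 30%.* That holds only for a full pack on the first postintervention day; with less in hand it can be met, as step 5 shows.
- *The primary outcome is compromised.* Openings are time-stamped, so a late upload alone does not change global adherence.

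**Conclusion.** The point holds in a conditional form. The article disagrees with itself on when monitors are read after the intervention. If reads follow refills and refills follow consumption, the two-consecutive-visits outcome is detected late or missed in patients who take all their monitored drugs badly or have only one. A second read as late as 207 days (30-day supply) or 621 days (90-day supply) at 29% adherence is the upper end of the range and assumes a full pack at the start of the phase; the lower ends are 103 and 310 days. With calendar reads the problem vanishes. The consequence is confined to one secondary outcome and the alert. It is worth correcting because the remedy for the outcome is cheap and works under either reading of the schedule.

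**What to change.** **Secondary outcome** (Secondary Outcomes; Data Analysis, Medication Adherence):

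- Compute adherence per drug from the stored time-stamped openings, in equal, prespecified calendar windows starting at the end of the intervention and identical for all patients.
- Count an event when two successive windows are below 30%.
- Count a patient withdrawn by the software alert before two windows are complete as having the event at the alert date. Otherwise the new definition would lose patients who met the plan's own event.
- Compare the counts over the 12 postintervention months common to both groups.

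**Alert:** reconcile Medication Adherence Intervention, Postintervention Monitoring Phase, and Participant Timeline and Data Collection on when monitors are read in the postintervention phase. No threshold, reading interval or stopping rule is proposed here.

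The cost is some reprogramming of data the monitors already hold and a wording correction. Analysed events will not coincide exactly with the software alerts, and data on a monitor that is never brought back remain lost.
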